### Database variables

A detailed review of all the data items collected by each of the participating networks has been conducted and the elements common to all networks (e.g. gestational age, birth weight, sex, etc.) included in a minimum dataset (see Additional file 1 for full list of data variables). Data items that are collected by all networks in slightly different formats (e.g., nosocomial infection, which can be defined by using a cut-off of 2 days, 3 days, or 7 days) have been standardized across all the networks by consensus of the network directors. Some networks already extract data from their databases according to the iNeo definitions, while others have agreed to redefine their original data formats as an ongoing process to ensure consistency and facilitate comparisons over time. The variable definitions have been mapped to the ICD-10 [36] and SNOMED [37] dictionaries.

### Ethics, data collection, and dissemination

All participating networks have obtained ethics/regulatory approval or the equivalent from their local granting agencies to allow for de-identified data to be sent to the iNeo Coordinating Centre at the Maternal-Infant Care Research Centre, Mount Sinai Hospital, Toronto, Canada. The Coordinating Centre has been granted Research Ethics Board approval for the development, compilation, and hosting of the iNeo dataset, and all networks have signed data transfer agreements with the iNeo Coordinating Centre. Privacy and confidentiality of patient and unit-related data will be of prime importance to the iNeo collaboration, and data collection, handling, and transfer will be performed in accordance with the Canadian Privacy Commissioner’s guidelines, the Personal Information Protection and Electronic Documents Act, and any other local rules and regulations. No data identifiable at the patient level will be collected or transmitted, and only aggregate data will be reported. For all stages of the project, participating units will be assigned a code by their own network prior to data transfer into the iNeo dataset so that units remain anonymous within the iNeo collaborative. Following data analysis, findings will be disseminated within networks by their own network coordination team and not by the iNeo central team.

Following completion of the study in 2017, the data will be kept at the iNeo Coordinating Centre for a further two years before being returned to the originating networks unless otherwise agreed by the member networks.

### Comparisons of neonatal outcomes between networks

#### Outcomes

The primary outcome for comparison between the networks will be a composite indicator of mortality or any of the four major neonatal morbidities (severe neurological injury, severe ROP, NEC, and BPD). Mortality will be defined as death due to any cause prior to discharge home. Severe neurological injury will be defined as ≥ stage 3 intraventricular hemorrhage (IVH) with ventricular dilatation according to the criteria of Papile et al. [38], or parenchymal injury (including periventricular leukomalacia) with or without IVH. Severe ROP will be defined as ≥ stage 3 according to the International Classification [39], or need for laser surgery or intraocular injections of anti-vascular endothelial growth factor agents. NEC will be defined as ≥ stage 2 according to Bell’s criteria [40] and BPD as oxygen requirement at 36 weeks post-menstrual age [41].

Secondary outcomes to be compared among iNeo member networks will include the individual morbidities of the composite outcome, as well as nosocomial infection defined as culture-proven sepsis (blood or cerebrospinal fluid positive for pathogenic organism) at >3 days or 72 hours postnatal age [42], patent ductus arteriosus requiring pharmacological treatment and/or surgical ligation, receipt of delivery room cardiopulmonary resuscitation, air leak syndrome, and resource utilization (length of stay and length of respiratory support). To account for potential differences in practices regarding discharge home and transfer to Level 2 community units, additional analyses will compare mortality by Day 28 after birth. All outcomes will be expressed as ratios with the denominator equal to all admissions to participating NICUs.

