### Rationale

Over the past 5 years, collaborations have been initiated between the CNN, NRNJ, ANZNN, and SNQ. The first ever population-based retrospective comparison between countries showed that a composite outcome of mortality or any major morbidity (bronchopulmonary dysplasia [BPD], severe neurological injury, ≥stage 3 retinopathy of prematurity [ROP], nosocomial infection [NI], and ≥ stage 2 necrotizing enterocolitis [NEC]) was lower in VLBW infants in Japan compared with Canada. In-depth analyses revealed higher rates of severe neurological injury, NEC, and NI among NICUs in the CNN, whereas rates of BPD and ROP were higher in NRNJ NICUs [30]. Comparisons between the CNN and the ANZNN for VPT infants identified that while there was no difference in mortality, the ANZNN had significantly lower rates of severe neurological injuries, ROP, NEC, and BPD, but higher rates of early onset sepsis and air leaks and longer mean length of stay [31,32]. Our latest comparisons indicated that rates of adverse outcomes at each gestational age were lower in Sweden compared with Canada (unpublished data).

Differences in the outcomes of VLBW and VPT infants between Canada and other countries could be due to any number of factors including differences in population characteristics, severity of illness, processes of care, or delivery of health care. Informal discussion has confirmed wide variations in these factors between networks. For example, compared with Canada, the use of non-invasive respiratory support is higher in Europe, the use of breast milk is higher in Japan and Scandinavia, and the use of echocardiography by neonatologists for hemodynamic monitoring is routine in Japan. Differences in the type of intervention and process of administration may underlie at least some of the variations in outcomes. In addition, there are extreme variations in health services delivery and receipt. For example, the number of outborn, very preterm infants is significantly lower in the ANZNN compared with the CNN [32]; the use of respiratory therapists is practically non-existent in European countries, whereas they play a prominent role in North American institutions; and shift work is more prevalent among junior doctors in Europe and Australia [33] compared with Canada.

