#### Adjustment for variations in baseline population characteristics between networks

Demographic characteristics and severity of illness are well known to impact neonatal outcomes [43] and are also likely to vary between networks. To prevent bias, these potential confounders will be controlled in analyses comparing network-level outcome rates. The common minimum dataset includes important predictors, such as gestational age, sex, plurality of pregnancy, and receipt of antenatal corticosteroids, which will be used to adjust analyses as appropriate. In addition, most networks collect various measures of ‘severity of illness’, such as CRIB [44], SNAPPE-II [45], or TRIPS [46] scores. These will be standardized within each network (assigned a score between 0 and 1) and adjusted for in analyses.

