#### Care-provision factors

Clinical practices represent the third and possibly most important set of characteristics that likely contribute to variation in outcomes. Variations in clinical practices are well known among neonatal communities [8]; however, no systematic prospective approach has determined, compared, and benchmarked variations associated with outcomes. Some of the key practice variations between centers and networks include referral practices (inborn vs. outborn) [62-64], differential use of the type of initial respiratory support [65-67], types and timings of surfactant administration [68], fluid management [69], timing of initiation of parenteral nutrition [70], use of donor milk, management of patent ductus arteriosus [71], availability and use of echocardiography, use of prophylactic interventions [72] (e.g., probiotics, high frequency oscillatory ventilation, phototherapy, and L-arginine), and the scope of involvement of parents.

Specific to each secondary outcome we will identify ‘top’ performing networks and networks with significant room for improvement. Subsequently, working groups of interested stakeholders from each network will be formed to determine methods to identify possible care provision practices related to such variations. Study methods will be similar to those described earlier, and will include annual snapshot surveys of each unit, detailed questionnaires specific to practices (e.g. parental presence, use of donor milk, diagnosis and management of hypotension, etc.), and in certain instances of outstanding success, a site visit with structured exploration of the practices in question. All methods of exploration will be conducted with directions from the iNeo Governing Board and Scientific Advisory Committee to protect privacy and confidentiality. Because individual unit information will not be disclosed to the iNeo Coordinating Centre, individual networks will be asked to identify willing members for such participation.

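### BPD is defined by oxygen requirement alone at 36 weeks, so infants on pressure support in room air are coded BPD-free, which can bias network comparisons of BPD and the primary composite by an unknown amount

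*Protocol article*

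**What the plan says.** The Outcomes section defines "BPD as oxygen requirement at 36 weeks post-menstrual age". It names no form of pressure support and does not say how an infant on CPAP or ventilation in room air is coded.

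BPD enters the plan in two places. It is part of the primary outcome, a "composite indicator of mortality or any of the four major neonatal morbidities (severe neurological injury, severe ROP, NEC, and BPD"). It is also compared separately, because the secondary outcomes include "the individual morbidities of the composite outcome". Under Care-provision factors, top-performing networks and networks with room for improvement are to be identified for each secondary outcome. The section on implementation and evaluation of practice changes uses reduction of BPD as its worked example.

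On respiratory support, the Rationale reports that "compared with Canada, the use of non-invasive respiratory support is higher in Europe", and Care-provision factors lists "differential use of the type of initial respiratory support" among the key practice variations. The adjustment section names baseline predictors such as "gestational age, sex, plurality of pregnancy, and receipt of antenatal corticosteroids", plus severity-of-illness scores. The only outcome that measures support itself is a separate secondary one, "resource utilization (length of stay and length of respiratory support").

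**The concern.** Apply the rule to three infants at 36 weeks post-menstrual age:

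- Infant A is on CPAP or a ventilator in room air: no BPD.
- Infant B is on low-flow nasal oxygen without pressure: BPD.
- Infant C breathes room air unsupported: no BPD.

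Infant A still depends on respiratory support but is scored like C and better than B. The error runs one way, since it can only lower BPD and composite counts. If the share of infants like A were equal in all networks, every rate would be lowered by the same amount and the absolute differences between networks would stand. If the share differs, part of an observed difference reflects mode of support and not lung disease.

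This project compares networks, labels their performance and then looks for practices associated with better outcomes. Respiratory-support practices are among the candidate exposures. When BPD is the outcome, exposure and outcome coding can be linked mechanically: a practice that replaces nasal oxygen with pressure in air lowers recorded BPD even if lung disease is unchanged.

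**Working it through.** **1. Reproduce the protocol's own yardstick.** Inputs: yearly eligible admissions in Table 1, times four years (2007–2010).

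- Canada: 4 × 2,700 = 10,800.
- All others: 4 × (23,400 − 2,700) = 82,800.
- Smallest network: 4 × 800 = 3,200. Largest: 4 × 7,700 = 30,800.

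All four match the section on statistical power for outcome comparisons. Power for two proportions, two-sided:

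Power = Φ[(|p1 − p2| − z × SE0) / SE1], with SE0 = √[p̄(1 − p̄)(1/n1 + 1/n2)], SE1 = √[p1(1 − p1)/n1 + p2(1 − p2)/n2] and p̄ the pooled rate.

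Solved for 80% power at alpha 0.05 (z = 1.96):

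| Comparison | Rate 1% | Rate 40% | Protocol states |
|---|---|---|---|
| Canada v all others | 0.0031 | 0.0141 | 0.004 to 0.02 |
| Canada v 3,200 | 0.0062 | 0.0277 | 0.007 to 0.03 |

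The protocol's figures are these values rounded up, so they are not in dispute. They serve only as a scale.

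**2. What size of artefact would matter?** At a 40% rate, the top of the protocol's range, the detectable difference is about 2.8 percentage points against a network of 3,200 and about 1.5 points against one of 30,800. A gap of that size in the share of infants on pressure support in room air would equal the whole detectable difference.

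**3. Chance of a false significant result.** The article gives no such share for any network, so the shares below are assumptions. Both networks have the same true rate (oxygen or pressure support counted). The recorded rate is the true rate minus the assumed share. For the composite, the share means infants with no other component. The Bonferroni column uses 28 pairs (8 × 7 / 2), alpha = 0.05/28 = 0.0018, z = 3.12.

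Worked line: true rate 40%, shares 1% v 3%, n = 10,800 v 3,200. Recorded rates are 0.39 and 0.37, p̄ = 0.3854, SE0 = 0.00980, SE1 = 0.00974. At alpha 0.05, Φ[(0.02 − 1.96 × 0.00980)/0.00974] = 0.53. At alpha 0.05/28, Φ[(0.02 − 3.12 × 0.00980)/0.00974] = 0.14.

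True rate 40%, Canada v one network:

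| Assumed shares | Gap | v 3,200, alpha 0.05 | v 3,200, alpha 0.05/28 | v 30,800, alpha 0.05 |
|---|---|---|---|---|
| 1% v 2% | 0.01 | 0.17 | 0.02 | 0.45 |
| 1% v 3% | 0.02 | 0.53 | 0.14 | 0.96 |
| 1% v 4% | 0.03 | 0.87 | 0.48 | about 1.0 |
| 2% v 6% | 0.04 | 0.99 | 0.84 | about 1.0 |

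At a true rate of 20%, v 3,200 and alpha 0.05, the same four gaps give 0.24, 0.73, 0.98 and about 1.0. With a gap of zero there is no artefact. These figures ignore clustering and covariate adjustment, as a simple two-proportion calculation does.

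**4. Composite.** An infant like A drops out of the composite only if alive and free of severe neurological injury, severe ROP and NEC. The composite therefore falls by no more than BPD does.

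**5. Adjustment.** The named covariates describe the infant at or near birth. They do not describe mode of support at 36 weeks, so they cannot restore an infant whom the outcome rule has coded negative.

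**The case against.** A reader might infer that networks using more non-invasive support do get lower BPD and composite rates from this rule. The article does not support that. The remark that "the use of non-invasive respiratory support is higher in Europe" is attributed to informal discussion and mentions neither 36 weeks nor room air, and the variation listed under Care-provision factors concerns initial support. No network's share is given, so a gap of zero cannot be excluded. A lower BPD rate with more non-invasive support could also be a true benefit. This objection stands: the article supports a possible bias and not a demonstrated one.

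It may also be tempting to conclude that the definition should be replaced. That goes too far. Counting any positive pressure makes BPD depend on CPAP policy in the other direction: a unit that keeps infants on CPAP in air for longer would record more BPD for the same lung disease. This also stands.

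Three further points carry some weight:

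- The Bonferroni correction planned for pair-wise comparisons makes a false finding less likely. It does so without removing the bias, and less effectively as the gap or the network grows.
- Length of respiratory support is compared separately, so replacement of oxygen by CPAP would be partly visible. Total duration does not show status at 36 weeks if support was intermittent.
- The article refers to standardized definitions and to Additional file 1, which is not at hand. Finer BPD coding may be there, although the Outcomes section gives no sign of it.

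Finally, practice changes also pass through working groups and a review of published evidence, so a BPD rate alone would not decide them.

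**Conclusion.** The concern holds as a risk of differential misclassification. As written, the rule codes infants on pressure support in room air as BPD-free. The protocol itself reports that non-invasive support differs between networks, and its baseline adjustment cannot correct outcome coding. The bias, where present, favours networks with more such infants at 36 weeks. It affects BPD fully and the primary composite to an equal or smaller extent.

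Its size cannot be established from the article. The probabilities in the table rest entirely on the assumed gaps of 1 to 4 points, on equal true rates and on independent infants. They show that a gap of a few points would be on the scale of the differences the study is powered to detect. They do not show that such a gap exists. A sensitivity analysis is warranted, and a change of the primary definition is not.

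**What to change.** Keep the cited oxygen-only definition of BPD as primary, and state explicitly how infants on CPAP or ventilation in room air at 36 weeks are coded. Add a prespecified sensitivity analysis that repeats the BPD and composite comparisons counting oxygen requirement or any positive-pressure support at 36 weeks post-menstrual age. Run it in the networks whose data give support status at that age. Report both versions side by side for the same networks, and flag any top or poor BPD label that changes between them.

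The cost is one definition line and one extra analysis. It may cover only a subset of networks, since the data are retrospective and the article confirms only length of support, not status at 36 weeks. The wider rule is itself sensitive to CPAP policy, so it serves as a check and not as a replacement. Agreement between the two versions would be reassuring. Disagreement would show that the BPD ranking depends on how support is counted.

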#### Comparisons between networks

For the primary composite outcome, each of its components and the additional secondary outcomes, initial crude rates, and associated 95% and 99% confidence intervals will be calculated and graphically displayed using ‘caterpillar plots’ to visually identify differences between networks. To adjust for multiple baseline characteristics, standardized outcome ratios will be computed using the ‘indirect standardization’ approach. Each network’s observed rate will be compared with the expected rate based on the total sample from all other networks to identify networks with rates significantly above or below average. For each outcome, the expected number of events will be computed as the sum of predicted probabilities from a multivariable model (logistic regression or zero inflated negative binomial models based on data distribution) derived using data from all other networks with adjustment for confounders. Network standardized outcome ratios will be graphically displayed using ‘funnel’ plots with 95% and 99% prediction intervals for comparison between networks.

A global comparison, as well as pair-wise comparisons between networks, will be performed using multivariate regression models adjusted for confounders. Statistical models will employ generalized estimating equations to adjust analyses for clustering of infants within networks. In addition, hierarchical random-effects regression models will be used to allow for variation at the network and unit level. Statistical significance will be evaluated by applying a Bonferroni correction to account for multiple pair-wise comparisons.

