The practice changes implemented by individual units within networks will be evaluated every 6 to 12 months depending upon each centre’s capabilities to collect and submit data. In addition to outcome indicators, process indicators will be developed based on the specific interventions implemented. These indicators will measure the short-term impact of practice change. For example, an intervention targeting early surfactant administration to reduce BPD will have process indicators for the time of first surfactant administration and the proportion of babies who received surfactant within the first 30 minutes after birth. The outcome of interest for this intervention will be reduction in the incidence of BPD. Safety and outcome improvements will be monitored within each unit and network using control charts and Chi-square tests for differences in outcome rates from baseline. Multivariable logistic regression analyses will pool data from units within each network to assess changes in outcomes over time with adjustment for potential confounders and important risk factors, and accounting for clustering.

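### Delivery-room resuscitation, a secondary outcome, falls under a blanket adjustment for illness severity; a score read at or after admission is not a baseline confounder for it

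*Protocol article*

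**What the plan says.** Four statements in the protocol article bear on this point.

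- **Outcomes.** The secondary outcomes to be compared among networks include "receipt of delivery room cardiopulmonary resuscitation". The denominator, "All outcomes will be expressed as ratios with the denominator equal to all admissions to participating NICUs", is thus the same for this outcome as for the others.
- **Adjustment for variations in baseline population characteristics between networks.** Illness severity and demographic factors are introduced together as influences on outcome, and then: "To prevent bias, these potential confounders will be controlled in analyses comparing network-level outcome rates". Most networks are said to hold a severity measure, "such as CRIB [44], SNAPPE-II [45], or TRIPS [46] scores". The rule for these is: "These will be standardized within each network (assigned a score between 0 and 1) and adjusted for in analyses". The preceding sentence, on gestational age, sex, plurality and antenatal corticosteroids, allows those predictors to be used where appropriate. The sentence on the severity scores has no such qualifier.
- **Comparisons between networks.** "For each outcome, the expected number of events will be computed as the sum of predicted probabilities from a multivariable model". That model is fitted on the data of all other networks with adjustment for confounders. Adjusted regression models for global and pair-wise comparisons are planned as well.
- **Same section.** Crude rates with 95% and 99% confidence intervals are planned for the primary composite, its components and the additional secondary outcomes.

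The article does not say when any of the three scores is read.

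**The concern.** A confounder in a comparison of networks should be a characteristic the infant brings to the event being compared. For most outcomes listed (for example retinopathy, bronchopulmonary dysplasia or length of stay), an illness score taken early in the NICU stay can reasonably play that part. Delivery-room resuscitation is different, because it is over before the infant is admitted. A score describing the admitted infant may carry the mark of the resuscitation itself, or of the condition in which resuscitation left the infant. Putting that score into the model conditions the outcome on something that may follow from it.

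At stake is the adjusted comparison for this one outcome. The standardized ratio is meant to flag networks whose rate is above or below average, and the regression models are meant to test differences between them. If the score responds to resuscitation, neither quantity compares infants who were alike at birth, and the two may disagree on the same data.

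**Working it through.** The article gives no figure on this point, so there is nothing to reproduce. The check has two parts.

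**1. Reading the sections together**

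1. The outcome occurs in the delivery room (Outcomes).
2. The analysed infants are admissions to participating NICUs (Outcomes). For every one of them the outcome therefore precedes admission.
3. Severity scores are to be adjusted for in comparisons of network-level outcome rates, and no outcome is exempted (Adjustment section).
4. An adjusted expected count is computed for each outcome (Comparisons section).

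Read literally, the model for delivery-room resuscitation includes the severity score. If the score is read at or after admission, it comes later than the outcome it is used to predict. Whether it is read then is a condition, because the article gives no scoring window.

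**2. What such adjustment can do: a simulation**

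None of the inputs comes from the article. They were chosen only to show the direction of the bias.

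- Illness at birth, U, is standard normal with the same distribution in both networks (200,000 infants in the network judged, 600,000 in the comparison group).
- Resuscitation Y follows logit P(Y = 1) = ln(0.04/0.96) − 0.4 + U + ln(2) × network. The true conditional odds ratio is 2, and the resulting rates are about 7.6% and 4.2%.
- The later score is S = U + g × Y + 0.7 × noise. A positive g means that resuscitated infants score as sicker.
- O/E is the observed rate divided by the mean predicted probability from a logistic model fitted in the comparison group. OR is the network odds ratio from a pooled logistic model. Both models use linear and squared terms of either U or S.

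The score was used raw, or ranked to 0–1 within each network. Ranking is one reading of the planned standardization. A linear rescaling with the same range in every network would behave like the raw score.

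| Scaling of S | g | O/E adjusted for U | O/E adjusted for S | OR adjusted for U | OR adjusted for S |
|---|---|---|---|---|---|
| raw | −1 | 1.84 | 1.83 | 1.99 | 1.90 |
| raw | 0 | 1.83 | 1.83 | 1.98 | 1.95 |
| raw | 0.5 | 1.85 | 1.80 | 2.01 | 2.01 |
| raw | 1 | 1.82 | 1.66 | 1.97 | 2.01 |
| raw | 2 | 1.85 | 1.39 | 2.01 | 2.13 |
| raw | 3 | 1.83 | 1.19 | 1.98 | 2.25 |
| ranked within network | −1 | 1.84 | 1.84 | 2.00 | 1.91 |
| ranked within network | 0 | 1.80 | 1.80 | 1.95 | 1.90 |
| ranked within network | 0.5 | 1.85 | 1.85 | 2.00 | 2.05 |
| ranked within network | 1 | 1.86 | 1.86 | 2.02 | 2.21 |
| ranked within network | 2 | 1.82 | 1.82 | 1.97 | 2.95 |
| ranked within network | 3 | 1.86 | 1.86 | 2.02 | 8.28 |

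Adjusting for illness at birth gives O/E of 1.80 to 1.86 and OR of 1.95 to 2.02 in every row. Adjusting for the later score gives three patterns:

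- With a raw score that resuscitation worsens, O/E moves towards 1 while OR rises somewhat.
- With a ranked score, every network has the same score distribution by construction. O/E therefore stays at the crude ratio, and the distortion appears as an inflated OR.
- With negative g, O/E barely moves and OR is slightly low.

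**The case against.** The case on the other side is substantial.

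- **The timing is not documented.** The article names the scores under a heading on baseline characteristics and gives no window. This stands, and it is why the point is conditional.
- **Models are built outcome by outcome, and the final covariate list may sit in an analysis plan.** This stands in part. An article may leave covariate lists to such a plan, but here it states a rule for the severity scores without exception, while the neighbouring sentence on other predictors leaves room for judgement.
- **Crude rates are planned, so a difference in resuscitation would remain visible.** That is true. But crude rates do not account for gestational age or other case mix, so they do not replace a comparison adjusted for birth factors.
- **Only one secondary outcome is concerned.** This stands and sets the weight of the point.

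A reader might go further in three ways that the article does not support. The first is that the adjustment hides real differences or pulls ratios towards 1: the table shows this for O/E with a raw score only. The second is that early practices, such as initial respiratory support or prompt surfactant, are over-adjusted in the same way. The sections on practice associations and on evaluating practice change refer to confounders and risk factors but do not name the severity score. The third is that the distorted ratios will decide which networks count as top performers. The section on care-provision factors names no metric for that choice.

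**Conclusion.** The point holds as a minor one. As written, the plan conditions a delivery-room event on an illness score of the admitted infant. If that score is read at or after admission, it is not a baseline confounder for resuscitation, and the adjusted comparison can be biased in either direction, depending on how the score is scaled and which model is used.

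The size cannot be derived from the article. The simulated values show that the distortion can be negligible or large, but they rest wholly on assumed inputs, above all on how strongly resuscitation changes the score. The primary composite is not affected by this ordering problem.

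**What to change.** In the section on adjustment for baseline population characteristics, make two additions.

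1. State when each network's severity score is read.
2. State that delivery-room resuscitation is adjusted only for factors fixed at or before birth that the networks collect: gestational age, birth weight, sex, plurality and antenatal corticosteroids. Leave any score read after resuscitation out of this model, or show it only as a sensitivity analysis.

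The cost is a sentence or two in the covariate rule, with no new infant-level data. The downside is somewhat less control of case mix for this one secondary outcome.
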